### Primary outcome

The primary outcome is the recovery of the PQRS at postoperative day 1 (POD1) (see the subsequent sections for details).

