### Post-operative Quality of Recovery Scale

The PQRS is a validated multidimensional PRO tool [29–31] designed to assess patients’ recovery to baseline status in the postoperative period (www.postopqrs.com). In every patient a baseline measurement of PQRS is performed prior to surgery. After surgery, the measurement of the PQRS is repeated at 15 min (T15) and at 40 min (T40) after arrival in the PACU, as well as in the ward on the morning of POD1 and POD3. The PQRS is a verbal survey tool that depicts recovery in the following five domains: physiologic, nociceptive, emotive, functional, cognitive, and also collects overall patient perspective. Each of these domains is assessed with multiple items on an ordinal scale and compared with baseline to evaluate recovery (see Table 2 for details). Recovery is a dichotomised outcome defined by a return to at least baseline values or better at each of the postoperative measurement time points. Overall recovery requires recovery in all domains being assessed, and failure in any domain results in failure of overall recovery.

**Table 2 Tab2:** Post-operative Quality of Recovery Scale (PQRS)

Domain	Variable	Score	Baseline	T15	T40	POD1	POD3
Physiologic	Blood pressure	1–3	+	+	+	+	+
Physiologic	Heart rate	1–3	+	+	+	+	+
Physiologic	Temperature	1–3	+	+	+	+	+
Physiologic	Respiration	1–3	+	+	+	+	+
Physiologic	SpO2	1–3	+	+	+	+	+
Physiologic	Airway	1–3	+	+	+	+	+
Physiologic	Agitation	1–3	+	+	+	+	+
Physiologic	Consciousness	1–3	+	+	+	+	+
Physiologic	Activity on command	1–3	+	+	+	+	+
Nociceptive	Pain	1–5 Likert	+	+	+	+	+
Nociceptive	PONV	1–5 Likert	+	+	+	+	+
Emotional	Sadness/depression	1–5 Likert	+	+	+	+	+
Emotional	Anxiety/nervousness	1–5 Likert	+	+	+	+	+
Functional	Stand	1–3	+	–	–	+	+
Functional	Walk	1–3	+	–	–	+	+
Functional	Eat/drink	1–3	+	–	–	+	+
Functional	Get dressed	1–3	+	–	–	+	+
Cognitive	Name, city and DOB	TF 0	+	–	–	+	+
Cognitive	Numbers forward	TF 2	+	–	–	+	+
Cognitive	Numbers backwards	TF 1	+	–	–	+	+
Cognitive	Word task: list	TF 3	+	–	–	+	+
Cognitive	Executive memory	TF 3	+	–	–	+	+
Overall patient perspective	Ability to work	1–5	–	–	–	–	+
Overall patient perspective	Ability to perform ADLs	1–5	–	–	–	–	+
Overall patient perspective	Clarity of thought	1–5	–	–	–	–	+
Overall patient perspective	Satisfaction anaesthesia care	1–5	–	–	–	–	+

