Online scale to assess multiple domains of postoperative recovery over time. Timeline: T15–15 min in PACU, T40–40 min in PACU Scoring: Physiologic 1–3; Nociceptive/emotional 1–5, Likert rating scale using a faces pictorial display; Functional: Scored as 3 easily, 2 with difficulty, 1 not at all; Cognitive: Performance variability tolerance factor (TF) is applied. Participants not included in subsequent analysis if baseline scores are equal to or less than the TF *PACU* post-anaesthesia care unit, *POD1* postoperative day 1, *POD3* postoperative day 3, *SpO2* blood oxygen saturation, *PONV* postoperative nausea and vomiting, *DOB* date of birth, *ADL* activity of daily living

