Differences in continuous variables between groups (IAP, IAV, LOS, inflammatory biomarkers) will be assessed by linear regression or with the Mann-Whitney *U* test (if the normal distribution assumption is rejected by the Shapiro-Wilks test). Differences in ΔP_rs_ between groups will be assessed by linear regression. A multivariable model introducing BMI, previous laparoscopic surgery and age will be fitted for predictive purposes.

Differences in the plasma disappearance rate of ICG are assessed by beta regression. Occurrences of cough or spontaneous movements during anaesthesia are assessed by logistic regression.

The relationship between IAP and IAV will analysed by linear interpolation from the individual IAP/IAV curves. The IAP before CO_2_ gas insufflation (IAP at volume zero) will be estimated by fitting multiadaptive linear regression splines to the IAV and IAP relationship. If a variable has a frequency of missing data > 5%, data will be imputed by the multiple imputation method.

As there is no ethically unacceptable risk related to the primary outcome analysed, there will be no planned interim analysis.

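### The blanket multiple-imputation rule would impute day-1 recovery for patients who have no PQRS because they were too ill to be assessed

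*Protocol article*

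**What the plan says.** The protocol article handles missing data in one sentence of the Analysis plan: "If a variable has a frequency of missing data > 5%, data will be imputed by the multiple imputation method". The sentence names no outcome, excepts none, and does not say whether items, domains or the overall result are imputed. The same section commits the primary endpoint to intention to treat, expects dropout of about 10%, and sets recruitment at 190 to leave 170.

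The section on the Post-operative Quality of Recovery Scale defines the outcome. It is binary: "Recovery is a dichotomised outcome defined by a return to at least baseline values or better at each of the postoperative measurement time points". The domains combine strictly: "Overall recovery requires recovery in all domains being assessed, and failure in any domain results in failure of overall recovery". The instrument is spoken ("The PQRS is a verbal survey tool that depicts recovery in the following five domains"), and the later assessments are made "as well as in the ward on the morning of POD1 and POD3".

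The footnote to Table 2 sets one group aside, on the cognitive tests: "Participants not included in subsequent analysis if baseline scores are equal to or less than the TF". Nothing in the article says how to classify a patient who cannot be assessed at a time point because of illness.

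**The concern.** A verbal questionnaire given on the ward will tend to be absent for a patient who on that morning is sedated, in intensive care, back in theatre or dead. Such a patient has not returned to baseline in any ordinary sense. The blank form carries information about the outcome, so the missing-at-random assumption behind standard multiple imputation is doubtful for exactly these patients.

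Imputation would borrow from patients who were well enough to be scored and would draw some of the unassessed as recovered. This affects the primary endpoint. The reported recovery proportion would be too high, and the treatment comparison could move either way, depending on which arm has more patients too ill to be scored.

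**Working it through.** **Can the rule reach the primary outcome?** Inputs from the Analysis plan: 170 evaluable patients, 10% dropout, 190 recruited.

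- The plan's own figure: 170 / (1 − 0.10) = 188.9, so 189. The stated 190 agrees.
- Trigger: 5% of 190 = 9.5, so the rule applies from 10 missing values.
- Expected dropout: 10% of 190 = 19. If 10 or more of these lack a day-1 PQRS, the rule applies. Once it does, every missing value is imputed, whatever its cause.

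**Does the level of imputation matter?** Not for a patient with no form at all. No domain has been observed to fail, so imputing items, domains or the overall result can each yield a recovered patient. It does matter for a partly completed form with a failed domain. There the overall result is already settled, and imputing the other domains and then deriving recovery keeps it a failure.

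**How many would be wrongly imputed?** The documents give no day-1 recovery rate and no count of unassessable patients, so all inputs below are assumptions. Take 95 per arm, m unassessed patients in an arm, all truly not recovered, and imputation at the recovery rate p of the assessed patients.

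- Wrongly imputed as recovered = m × p. With m = 5 and p = 0.40: 5 × 0.40 = 2 per arm.
- Overstatement of the arm's recovery proportion = m × p / 95 = 2 / 95 = 2.1 percentage points.
- Five per arm is 10 of 190, which just meets the trigger.

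**What happens to the odds ratio?** Assume that assessed controls recover in 20% to 70% and that the odds ratio among assessed patients is the plan's 2.65. Intervention recovery is then 2.65p / (1 − p + 2.65p), or 39.8% to 86.1%. Imputation leaves the odds ratio at 2.65. Scoring the unassessed as not recovered multiplies each arm's rate by (95 − m) / 95.

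| Unassessed, control / intervention | Imputed as recovered, control | Imputed as recovered, intervention | Odds ratio, imputed | Odds ratio, scored not recovered |
|---|---|---|---|---|
| 5 / 5 | 1.0 to 3.5 | 2.0 to 4.3 | 2.65 | 2.59 to 2.24 |
| 10 / 10 | 2.0 to 7.0 | 4.0 to 8.6 | 2.65 | 2.54 to 2.00 |
| 10 / 5 | 2.0 to 7.0 | 2.0 to 4.3 | 2.65 | 2.78 to 2.64 |
| 5 / 10 | 1.0 to 3.5 | 4.0 to 8.6 | 2.65 | 2.37 to 1.70 |

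Ranges run from 20% to 70% control recovery. Imputation gives the larger odds ratio in three rows. With more unassessed controls it gives a smaller or practically equal one. If assessed patients recover equally in both arms (30% to 70%), with 10 controls and 5 intervention patients unassessed, imputation gives 1.00 and failure scoring gives 1.08 to 1.17.

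**The case against.** A reader might infer that the plan overwrites known failures: patients with one failed domain and another missing. The documents do not support that. The rule imputes only missing data, and under the scale's definition "failure in any domain results in failure of overall recovery", so these patients' result is not missing. Harm would arise only if the overall result were blanked whenever any domain is missing and then imputed directly, and the article nowhere says so. For these patients the fix only confirms the order of derivation.

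A reader might also infer that the plan's own definition already makes the too-ill patient a failure. It does not say so: overall recovery is defined over the domains being assessed. That such patients are not recovered is a clinical judgement, though a safe one.

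Three further objections have force.

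- The physiologic domain includes airway, consciousness and activity on command. A sedated patient could be scored on these by an observer and so be an observed failure, which shrinks the unassessable group.
- The only dropout cause named is conversion to open surgery, the main one in the previous study, and this need not prevent a day-1 assessment. The 19 expected dropouts are therefore not 19 patients too ill to be scored.
- The article says that a statistical analysis plan was specified before enrolment. It is not shown, and it may refine the rule.

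The last objection does not remove the point. Detail left to an analysis plan would be no finding, but here the article states a rule, and applied as stated it gives the wrong treatment to an identifiable group on the primary endpoint.

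**Conclusion.** The point holds in limited form. The missing-data rule covers the primary outcome without exception, can be triggered at the plan's own dropout allowance, and would then impute recovery for patients unassessed because of illness. For them missing at random is not credible, and the result overstates recovery.

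The size cannot be fixed from the documents. About 2 patients, or 2.1 percentage points, per arm is an illustration. It rests on 5 unassessable patients per arm, 40% recovery, and imputation at the rate of assessed patients. An imputation model using the recovery-room scores or complications could draw fewer as recovered. After scheduled surgery in ASA I to III patients, the number too ill on day 1 may also be smaller. No claim that the rule favours one arm is supported, because the split of missing data by arm is not given.

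**What to change.** Replace the sentence in the Analysis plan with a rule in three steps:

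1. Derive overall PQRS recovery before any imputation.
2. Score as not recovered any patient with an observed failed domain, and any patient who could not be assessed at that time point for a medical reason (for example death, sedation, intensive care or reoperation).
3. Multiply impute only domains missing for non-medical reasons in patients with no failed domain, at domain level, and then rebuild overall recovery.

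Record the reason for every missing PQRS in the case report form, so that step 2 can be applied without judgement after the fact. The plan already undertakes to collect reasons for dropout, so this adds one code. The reported recovery rate will be slightly lower.

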### Adverse events

All adverse events (AEs) or serious adverse events (SAEs), related to the study medication or not, will be followed up by the investigators and documented in the electronic case report form (eCRF) up to 28 days after the end of the intervention period. All SAEs will be notified to the Steering Committee and promoter of the study as soon as the researcher has knowledge of the SAEs, but not more than 24 h after the researcher becomes aware of the event.

### Auditing

Sites may be subject to audits, independent ethics committee (IEC)/Institutional Review Board (IRB) review and regulatory inspection(s). Local investigators will provide direct access to the source data documents (see Additional file 4 for full details).

### Ethics and dissemination

The study will be carried out according to a protocol reviewed and approved at a national level by the IRB of Hospital Universitari i Politècnic La Fe, Valencia, Spain, and Agencia Española del Medicamento y Productos Sanitarios (AEMPS). The study has been registered at ClinicalTrials.gov (identifier NCT02773173, May 16, 2016) and EudraCT (2016-001693-15), and is conducted in accordance with the Declaration of Helsinki on ethical principles for medical research in human subjects, adopted by the General Assembly of the World Medical Association (1996). Data management, monitoring and reporting of the study are performed in accordance with the International Conference on Harmonisation (ICH) Good Clinical Practice (GCP) guidelines (CPMP/ICH/135/95) and the regulatory requirements for participating institutions by the Spanish Clinical Research Network (SCReN). Investigators collect a written informed consent form in compliance with the GCP recommendations to the patient or his/her legal representative if the patient’s clinical conditions do not allow him/her to review and approve it. Investigators provide a copy of the signed informed consent form to each subject and keep a copy in the subject’s study file. This study protocol is reported following the Standard Protocol Items: Recommendations for Interventional Trials and Patient-Reported Outcomes (SPIRIT-PRO) guidelines [24, 25].

The results of the study will be communicated through the portal of the European Medicines Agency and will be sent for publication in a peer-reviewed medical journal. Authorship will be based on International Committee of Medical Journal Editors (ICMJE) criteria. No professional writer will be involved. After publication of the primary results, upon request, the pooled dataset will be available for all members of the IPPCollapse-II study group for secondary analysis, after judgement and approval of the scientific quality and validity of the proposed analysis by the Steering Committee. Access to source data will be made available through national or international anonymised datasets upon request and after agreement of the IPPCollapse-II Steering Committee.

## Discussion

This study is the first randomised clinical study that tests the hypothesis that an individualised pneumoperitoneum pressure strategy focusing on using the lowest possible IAP, compared to a conventional pneumoperitoneum pressure strategy, improves recovery after laparoscopic colorectal surgery. This study uses the PQRS as well as the occurrence of postoperative complications until postoperative day 28 and also hospital LOS. Furthermore, we assess process-related outcomes like IAP and IAV during pneumoperitoneum and associated ventilator parameters. A strong multidisciplinary commitment between members of the perioperative team, consisting of surgeons and anaesthesiologists, makes this complex study feasible.

The IPPCollapse-II study has several strengths. Its prospective design will allow high accuracy of data to be collected, and its sample size allows us to draw valid conclusions. Selection of PROs as the primary outcome of this study facilitates the translation into clinical practice, since these outcomes are readily and easily perceivable by both patients and healthcare providers. To the best of our knowledge, this is the first multicentre randomised clinical study evaluating the clinical effect of a tailored IAP management. The surgeon will remain blinded for the IAP, allowing us to titrate the IAP to the lowest possible level, i.e. the level at which surgeons have adequate workspace. Furthermore, we aim to describe the relationship between the IAP and actual IAV at which surgery is performed. This could lead, on the one hand, to gathering evidence towards establishing a volume threshold (e.g. the actual workspace) for colorectal laparoscopic surgery to replace the standard pressure threshold, and on the other, to describing the abdominal pressure-volume relationship in a first attempt to achieve something similar to our understanding of lung dynamics during ventilation. Additionally, we directly link the respiratory system and abdomen by assessing the IAP and respiratory driving pressure relationship. This could bring us a step further in achieving protective ventilation in the operating room.

The study proposed here differs from previous studies on this topic. Most studies so far have evaluated the individual components of the multifaceted strategy and are largely focused on surgical conditions and not patient-centred outcomes. Also, they generally find minor gains from abdominal prestretching or patient positioning optimisation and offer inconclusive results or marginally positive effects for the level of neuromuscular blockade [35–45]. Two studies find IAP titration useful in decreasing conventional IAP management, but they do not focus on clinical outcomes [46, 47].

To our knowledge, only one study so far focused on quality of recovery, using the Quality of Recovery 40 (QoR-40), a 40-item questionnaire on quality of recovery from anaesthesia [36]. This study, comparing surgery at low IAP (6 mmHg) versus standard IAP (12 mmHg) during laparoscopic donor nephrectomy under deep neuromuscular blockade, found no differences in QoR-40 score. Of note, in this study surgeons were not blinded for the IAP and in 25% of patients surgery had to be converted to the standard pressure, probably due to the surgeon’s learning curve. We recently performed the IPPCollapse-I study, in which we evaluated the feasibility of the intervention being tested in the present study [23]. The intervention was found to be safe and highly feasible and resulted in an acceptable workspace at low IAP in most patients. We did not look at patient outcomes in the preceding study.

The PQRS has been successfully tested in previous studies to evaluate differences in recovery [48–51]. We acknowledge that finding differences in PROs by PQRS modifying a single strategy in a high quality environment could be difficult [52–54]. In order to evaluate minor differences in recovery, mainly in laboratory data, we perform three substudies. Levels of biomarkers (neutrophil-lymphocyte ratio, C-reactive protein, interleukin-6 and procalcitonin) in the postoperative recovery period are linked to immunosuppression and postoperative complications [55, 56]. Untargeted metabolomic intraoperative analyses of blood samples and peritoneum biopsies allow us to depict differences between groups in the intraoperative setting and generate a hypothesis for new studies. PDR_ICG_ has been used successfully to evaluate hepatic perfusion in critically ill patients with intra-abdominal hypertension [28] and could reveal differences in hepatic perfusion during pneumoperitoneum in this study.

This study has limitations. We exclude ASA IV patients, who could benefit more from working with low IAP. Since we test a multifaceted strategy, it will remain uncertain which part of the strategy will have the largest impact. In fact, it could very well be that not all parts have the same magnitude of effect, and it is even possible that some parts have negligible  effects. Of note, reversal of neuromuscular blockade with sugammadex instead of neostigmine could improve PQRS recovery at T40 although not at POD1 or POD3. Surgeons, blinded for the actual IAP, will evaluate surgical conditions in a practical dichotomous manner as adequate or not, depending on whether any corrective action is needed. This way of measurement might make comparisons with other studies difficult, such as those using the Leiden-Surgical Rating Scale. The anaesthesiologists collecting the PQRS evaluations are not blinded for the assigned strategy, as they were present during the surgical procedure. However, the risk of bias will be very low, as the PQRS is a ‘patient-reported’ outcome, and the patients remain blinded at all times, including the time at which the PQRS score is collected. We calculated the sample size of our study on PQRS differences; thus, our sample could be underpowered for some secondary outcome that can potentially require a larger sample. In conclusion, the IPPCollapse-II study is designed to test if an individualised pneumoperitoneum pressure and optimised management versus conventional care will affect the outcome of patients undergoing colorectal laparoscopic surgery using relevant patient-centred outcomes.

### 3.1. Trial status

The Protocol Version is Version 1.0; June 7, 2016. A competent IRB, as detailed in the text, approved this version of the protocol. Recruitment began on February 1st, 2017. The expected date for recruitment completion is October–November 2018.

## Abbreviations

ASA: American Society of Anesthesiologists
BMI: Body mass index
eCRF: Electronic case report form
GCP: Good Clinical Practice
IAP: Intra-abdominal pressure
IAV: Intra-abdominal volume
IPPCollapse: Individualized Pneumoperitoneum Pressure in Colorectal Laparoscopic Surgery versus Standard Therapy
IRB: Institutional Review Board
LOS: Length of (hospital) stay
PACU: Post anaesthesia care unit
PDR_ICG_: Plasma disappearance rate of indocyanine green
PEEP: Positive end-expiratory pressure
POD: Postoperative day
PQRS: Post-operative Quality of Recovery Scale
PRO: Patient-reported outcome
PTC: Post-tetanic count
SCReN: Spanish Clinical Research Network
SPIRIT: Standard Protocol Items: Recommendations for Interventional Trials
TOF: Train of four
UPLC: Ultra performance liquid chromatography
ΔP_rs_: Respiratory system driving pressure
